### Strategies to improve adherence to interventions {11c}

The Correctional Officer on secondment as the Project Officer will deliver the supplements to the enrolled prisoners and watch them taking the supplements to ensure compliance and therefore monitoring adherence to the study protocol. Adherence will be recorded for each week, with reasons for a lack of adherence recorded. Changes in participant’s omega-3 levels will also be used to determine adherence to treatment.

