## Interventions

### Explanation for the choice of comparators {6b}

The algal DHA-O capsules are ~ 1 g with 509.2 mg/capsule DHA/EPA (i.e. DHA 324 mg/capsule and EPA 185.3 mg/capsule), hence providing a daily dose of 1091 mg omega-3 (694 mg DHA and 397 mg EPA). No intervention has assessed blood levels of omega-3; hence, the use of a placebo is permitted [44]. The placebo capsules are a corn/soy oil blend and are identical in size and colour to the active capsules.

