### Intervention description {11a}

The Correctional Officer on secondment as the Project Officer will deliver the supplements to the enrolled prisoners on Mondays, Wednesdays and Fridays, and they will watch participants swallow the supplements to ensure compliance. Supplements will be provided over a 16-week duration, the average supplement duration of the 2 previous studies [2, 3]. Baseline and post-intervention measures include IBOS, institutional records of reprimands or misconduct, questionnaires and measure of muscle strength, and blood samples to measure the erythrocyte omega-3 index levels will also be used as a measure of compliance. The questionnaires are demographic (in house), Aggression Questionnaire (AQ) [45]; Browns Attention Deficit Disorder Scales (BADDS) [46]; Conners’ Attention Deficit Hyperactivity Disorder (ADHD) [47]; The Barratts Impulsiveness Scale-11 (BIS-11) [48]; Depression, Anxiety, Stress Scale (DASS-21) [49]; Wellness Questionnaire - the Short Form-36 [50, 51]; plus customised questions on sleep.

The prisoners will also be asked at the end of the trial which treatment they thought they were on.

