## Statistical methods

### Statistical methods for primary and secondary outcomes {20a}

In the simplest case, this study is designed to determine the difference between groups as proportion of responders to the treatment allocation. This analysis will be performed using a generalised linear mixed model adjusted for clustering by prison. IBOS scores will also be analysed using a form of generalised linear mixed model or generalised additive mixed models depending on the final distribution of the IBOS scores. These models also allow for the correlated nature of repeated measures over time and the correlation between prisoners from the same institution. Secondary measures will be analysed using linear mixed, or generalised linear mixed models again depending on the distributional form of the variable. These analyses will be conducted using STATA or R.

The data will also be analysed according to the change in the omega-3 index [24] as recommended by ISSFAL [24].

Our policy implementation is based on the primary outcome measure, the IBOS. The secondary outcome measures are hypothesis generating.

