### Methods for additional analyses (e.g. subgroup analyses) {20b}

A priori, a subgroup per protocol analysis is planned for those participants deemed to be compliant with treatment. Subgroup analysis that will be considered include 80% compliance to capsule regime, age as a covariate, per change in omega-3 as recommended by the ISSFAL [24] and the Aggression Questionnaire—high vs low dispositional aggression.

The covariates that might be adjusted for include baseline DASS scores and SF-36 scores. It is acknowledged that reactive aggression is influenced by depression, anxiety and stress and this will be identified through the DASS. The dispositional ‘satisfaction’ will be assessed via the SF-36. With respect to ADHD, we hypothesise a mediating role of ADHD in aggressive behaviour.

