## Discussion

At least 45% of prisoners in Australia are incarcerated for violent offences [67]. Approximately 46% of prisoners have experienced a mental health disorder [68]. The rate of prisoner on prisoner assault reported in NSW and QLD prisons is 34% [69].

Prisoners cost the nation $2.6 billion in 2013–2014 after expenses, with the average daily cost per prisoner exceeding the average Australian’s daily income [70]. Should the intervention reduce aggressive behaviour by 25%, the estimated impact upon institutional violence would be an 8.5% reduction based on extant assault prevalence rates (34%). Some estimations of cost savings across prison populations nationally would suggest up to $236 million/year (at a conservative $8500 per aggressive prison patient prevented). This intervention also has potential to enhance overall prisoner health outcomes and if omega-3 use is maintained post-incarceration to reduce violent recidivism.

Our feasibility study showed that prisoners are 4.3 times more likely to have an IBOS of > 2, if they are below the cutoff of 6% omega-3 index [38] but this does not show causality. This multi-centre trial is adequately powered to demonstrate the effect of n-3 LCPUFA on aggressive behaviour in adult male prisoners. The strengths of this study include the IBOS, measuring n-3 LCPUFA levels in the blood and, after demonstrating efficacy, rolling out into policy and practice and the health economics. The IBOS eliminates cross- and intra-jurisdictional variations in reprimands, robustly accounting for prisoner aggressive behaviours. The blood n-3 LCPUFA assessments will verify that the reduction in aggressive behaviour is related to an increase in n-3 LCPUFA. Once we demonstrate efficacy, we will translate into policy and practice across all jurisdictions in Australia. Given the high costs associated with prisoner aggressive behaviour, substantial cost savings are expected.

Our research team has the track record to navigate studies through the ethics approval process, as evidenced by the feasibility studies and publication outcomes [7, 53]. This research will be carried out in accordance with the Declaration of Helsinki [44] and the Australian National Statement on Ethical Conduct in Research Involving Humans [71]. This research will follow the CONSORT guidelines and is registered with the Australian New Zealand Clinical Trials Registry.

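### Change in omega-3 index does not measure adherence equally in the two arms, and an analysis by that change is observational, so it cannot verify the link to aggression

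*Protocol article*

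**What the plan says.** The protocol article has two measures of adherence. The first is watched dosing: "Adherence will be recorded for each week, with reasons for a lack of adherence recorded" (Strategies to improve adherence {11c}). The second is the blood index. The same section says that changes in a participant's "omega-3 levels will also be used to determine adherence to treatment", Intervention description {11a} says that "blood samples to measure the erythrocyte omega-3 index levels will also be used as a measure of compliance", and Table 1 lists erythrocyte fatty acid analysis under compliance.

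On the comparator, {6b} states: "The placebo capsules are a corn/soy oil blend and are identical in size and colour to the active capsules". Section {33} makes participation conditional on not buying additional fish or n-3 supplements during the trial.

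Two analyses draw on these measures.

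- **Per-protocol.** "A priori, a subgroup per protocol analysis is planned for those participants deemed to be compliant with treatment" ({20b}, repeated in {20c}). No rule says how the two measures combine or how the index applies to placebo. Section {20b} lists 80% capsule compliance and change in omega-3 as separate items among the subgroup analyses to be considered.
- **Change in index.** "The data will also be analysed according to the change in the omega-3 index" ({20a}).

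The Discussion then concludes: "The blood n-3 LCPUFA assessments will verify that the reduction in aggressive behaviour is related to an increase in n-3 LCPUFA". The primary analysis is by intention to treat ({20c}).

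**The concern.** A man who takes every corn/soy capsule and keeps to the purchase restriction should show little rise in his index. Judged by index change, he looks the same as a placebo man who took nothing. In the active arm the same measure does separate takers from non-takers. Men who take capsules reliably may also be calmer men, so a measure that removes non-takers from one arm only can create a benefit where there is none.

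The analysis by change in index has a related fault that does not depend on how the per-protocol set is defined. How far the index rises is settled after randomisation, partly by the man's own behaviour. Comparing men with large and small rises is therefore not a randomised comparison. The Discussion rightly says that the feasibility association does not show causality, but a within-trial correlation has the same limit. At stake is the mechanistic claim, which the Discussion sets beside the rollout into policy.

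**Working it through.** **Inputs from the protocol article.** Active dose 1091 mg/day of DHA plus EPA and corn/soy placebo ({6b}); 1:1 allocation ({8}); at least 6 centres (Study setting); 600 recruited, 360 completing, about 40% attrition, ICC 0.03, difference 25%, 80% power, alpha 0.05 ({14}). The article gives no non-adherence rate, no responder rates and no expected index rise, so those values below are assumptions.

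**The plan's own figure, used only as a yardstick.** 360 / (1 − 0.40) = 600. With 6 centres of 60 completers, the design effect is 1 + (60 − 1) × 0.03 = 2.77. Assumed responder rates of 25% and 50% (two-sided, continuity-corrected) need 66 per arm. Then 66 × 2 × 2.77 = 366 completers, and 366 / 0.60 = 610 recruited, close to the stated 360 and 600. So 25% works as an absolute difference of 25 points.

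**1. One common index threshold.** I used a null simulation of 2,000,000 participants per scenario. In the scenarios of interest one prognostic factor drives both adherence and response. All its parameters are assumed, so it shows direction and rough scale only. About 0.6% of placebo men reached a 1.5-point rise, against 72% to 76% of active men. With 360 / 2 = 180 completers per arm, that is 0.006 × 180 ≈ 1 placebo man against 130 (0.72 × 180) to 137 (0.76 × 180) active men. The placebo set is nearly empty.

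**2. A threshold on the active arm only.** Let there be no treatment effect. Let *f* be the non-adherent share in each arm, *p* the responder rate among adherers and *p − d* the rate among non-adherers.

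- Placebo, everyone kept: (1 − f)p + f(p − d) = p − fd
- Active, adherers only: p
- False difference: **f × d**

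| f (assumed) | d (assumed) | f × d | Share of the 25-point difference |
|---|---|---|---|
| 20% | 20 points | 4 points | 16% |
| 30% | 20 points | 6 points | 24% |
| 40% | 20 points | 8 points | 32% |

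For given *f* and *d* this is an upper bound: it assumes the index sorts the active arm perfectly and that no placebo man is removed by any rule.

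In the simulation, a 1.5-point threshold on the active arm alone gave false differences of 1.6 to 5.6 points, depending on how prognostic adherence was. With the strongest link, stricter thresholds of 2.0 and 2.5 points gave 8.5 and 11.4. The last figure exceeds 8 because that threshold keeps only 33% of the active arm, so the removed share is 67% and the implied gap is 11.4 / 0.67 = 17 points.

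**3. The same capsule rule in both arms.** Both arms then have rate p and the difference is 0. The simulation agrees: with at least 80% of capsules taken in both arms, the contrast was within 0.2 points of zero in every scenario. Keeping that rule and adding an index threshold in the active arm gave about 0 at 1.5 points, 0.6 at 2.0 and 1.1 at 2.5 (the last two with the strongest link).

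**4. Analysis by change in index.** Under the same null, comparing the top with the bottom quartile of rise within the active arm gave false differences of 9 to 28 points. The upper end exceeds the design difference.

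**5. When the bias vanishes.** With no factor linking adherence to response, every contrast above was about 0. The intention-to-treat contrast was about 0 throughout.

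**The case against.** The strongest reply is that the article fixes no index-based rule. The adherence sentence stands in a section on strategies to improve adherence, the analysis sections never ask for a rise, and the only threshold named is 80% of capsules, which treats the arms alike. An exact per-protocol definition is commonly left to the analysis plan. This stands in part. A reader might infer that an index rise is required for the per-protocol set, and the text does not say so. It does say, in more than one place, that the index is an adherence measure, and it does not tie the 80% threshold to the per-protocol set. The unequal reading is therefore open but not mandated.

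A reader might also infer that only active capsules can raise the index. That is too strong. Other dietary or non-study omega-3, or measurement variation, can raise it on placebo, and such a rise usefully flags contamination.

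The Discussion says the reduction is *related to* the increase, not caused by it. That is fair, so it should not be read as an outright causal claim. But *verify* promises more than a correlation can deliver, particularly just after the causality caveat on the feasibility data.

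The 4 to 8 points rest on values from nowhere in the article. The roughly 40% in {14} is attrition, not missed capsules under watched dosing. This stands, and the figures are only an illustration and an upper bound.

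Finally, a reader might infer that the main result is biased. It is not: the primary analysis is by intention to treat, and the sample size does not depend on this point.

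**Conclusion.** The concern holds in two parts of different firmness.

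- **Firm.** The analysis by change in index is stated in {20a} and listed again as a subgroup in {20b}. It conditions on a post-randomisation variable, is observational, and cannot verify the link.
- **Conditional.** Index change measures adherence unequally in the two arms. If it enters the per-protocol set, a common threshold nearly empties the placebo side, and a threshold on the active arm alone biases the contrast whenever adherence is prognostic. The size depends on assumed inputs. The bound f × d gives 4 to 8 points in the cases shown, and about 1 point or less remained in the simulation when the 80% capsule rule was also applied to both arms.

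The intention-to-treat primary analysis and the sample size are unaffected. The change should be made because it is cheap and protects the supporting analyses; the trial's main conclusion does not depend on it.

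**What to change.** 1. Define the per-protocol set in both arms by one observed-capsule rule, using the 80% threshold already named and the weekly records of the blinded Project Officers. State that a rise in the index does not define the set. It remains a post-randomisation set, so keep it supportive.
2. Report index change by arm as evidence of uptake on active and contamination on placebo.
3. Label the analysis by change in index exploratory and observational. Optionally add an analysis with randomised arm as instrument for index change, and state its downsides: a wider interval, the assumption that allocation acts only through the index, and missing post-intervention blood (at about 40% attrition, up to 600 − 360 = 240 men).
4. For any omega-3 subgroup, use the baseline index, which is already measured and used in the blocking ({16a}).
5. In the Discussion, change *will verify* to *will explore whether*.

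Items 1, 2, 4 and 5 change wording only and need no new data. The optional analysis in item 3 costs analyst time and the assumptions listed.

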### Relevant concomitant care permitted or prohibited during the trial {11d}

There are no additional requirements or changes to the participants’ routine other than consumption of the capsules and restriction to buy-ups, as described above. Participants will continue to attend all their scheduled activities such as work and education during the intervention.

Due to the ongoing SARS-Cov-2 pandemic, we, as well as, each Correctional Centre site have developed their own COVID19 safe plan. We submitted these COVID safe plans through an amendment to our ethics committees, and we have received approval from Our University of Wollongong Work Place and Health Safety & Ethics Committees.

### Provisions for post-trial care {30}

There are no expected harms resulting from the trial. All participants will be provided with a post-trial educational package to enable informed independent decisions on the maintenance of dietary/supplemental use of n-3 LCPUFA.

## Outcomes {12}

### Primary outcome measure

Aggressive behaviour will be assessed by the IBOS (Table 1) reported as a single measure, in addition to the number and severity of reprimands with both measures explained below.

**Table 1 Tab1:** Summary of the study outcome measures and methods

Variables	Methods	Who completes the task?
Primary outcome measure		
Aggressive behaviour	Converting routinely collected case notes into a numerical score of aggressive behaviour using the IBOS ([name], [name], [name]. The Inmate Behaviour Observation Scale (IBOS): A measure of prisoner aggression and violence based on inmate case notes, in preparation/forthcoming)	Correctional Officer on secondment as a Project Officer
Secondary outcome measures		
1. Aggressive behaviour	Counting the routinely collected reprimands into a numerical score and noting them as aggressive or non-aggressive	Correctional Officer on secondment as a Project Officer
2. Questionnaires		
Aggressive behaviour	Aggression Questionnaire [45]	Study participant with or without assistance from the Project Officer
Attention deficit disorder	Brown Attention Deficit Disorder Scales (BADDS, [46])	Study participant with or without assistance from the Project Officer
Attention deficit hyperactivity disorder	Conners’ Attention Deficit Hyperactivity Disorder (AHDH, [47])	Study participant with or without assistance from the Project Officer
Depression and anxiety	21-item Depression and Anxiety Stress Scale (DASS, [49])	Study participant with or without assistance from the Project Officer
Impulsivity	Barratt Impulsiveness Scale (BIS-Brief, [48])	Study participant with or without assistance from the Project Officer
Demographic questionnaire	In-house demographic questionnaire	Study participant with or without assistance from the Project Officer
Health questionnaire	SF-36 [50, 51] general health questionnaire, with additional questions on sleep	Study participant with or without assistance from the Project Officer
Secondary outcome measures		
3. Muscle strength	Dynamometer [52]	Correctional Officer on secondment as a Project Officer
Tertiary outcome measures		
1. Improved engagement in rehabilitation programmes	Completion of programmes and attrition of programmes	Manager of Offender Services & Programs (MOSP)/Manager Offender Development (MOD) will assist the Project Officer
2. Recidivism		CIG DG and Corrective Services Head Office
Other assessments		
Compliance	Erythrocyte fatty acid analysis [7]	CIA BJM and Research Fellow CHC
	Compliance as noted by the Project Officer	Correctional Officer on secondment as a Project Officer

#### Inmate Behaviour Observation Scale (IBOS)

Actual instances of hostile and aggressive behaviour are routinely recorded as prisoner incident reports, where an officer considers the behaviour substantial enough to warrant sanction. However, the intensity of such behaviour required to warrant sanction fails to capture the range and diversity of hostile and aggressive behaviours and thus results in a low incidence rate. Further, different jurisdictions have developed different metrics for the classification of behavioural disorder. Thus, ([name], [name], [name]. The Inmate Behaviour Observation Scale (IBOS): A measure of prisoner aggression and violence based on inmate case notes, in preparation/forthcoming) developed a generic behavioural observation rating scale (IBOS) for use across jurisdictions. The IBOS is a 7-point scale which classifies prisoner behaviours across an 8-week period using data derived from individual prisoner case notes. Case notes are routinely recorded by custodial and non-custodial staff in the Offender Integrated Management System (OIMS) database to report and capture a majority of significant observations and interactions with prisoners. A score of − 1 is applied to all instances recorded in that week of *pro-social behaviour*, while a score of 0 is given if there were no behaviours of significance recorded. Thereafter, instances of hostile/aggressive behaviour are scored from 1 (non-compliant) to 5 (physically aggressive), with each level of hostility/aggression operationally defined and illustrated by examples. Thus, higher scores are associated with greater levels of aggressive behaviour. Inter-rater reliability of the IBOS was 0.844 for repeat raters ([name], [name], [name]. The Inmate Behaviour Observation Scale (IBOS): A measure of prisoner aggression and violence based on inmate case notes, in preparation/forthcoming). The IBOS is a validated tool that can be used across jurisdictions. The IBOS is significantly correlated with institutional records of misconduct or reprimands ([name], [name], [name]. The Inmate Behaviour Observation Scale (IBOS): A measure of prisoner aggression and violence based on inmate case notes, in preparation/forthcoming) which are the most common measure of aggression in prison studies. The IBOS has been found to significantly correlate with both the Aggression Questionnaire (AQ) and the Brown’s Attention Deficit Disorder Scales (BADDS) [7], and given that the AQ and the BADDS are also significantly correlated [53], this adds to its construct validity.

#### Number and severity of reprimands

If an act of aggressive behaviour warrants a reprimand, they are recorded in the OIMS database by Correctional Officers. The reprimands will be extracted from the OIMS system by the Project Officer and classified as violent or non-violent cases.

### Secondary outcome measures

#### Psychological assessments—questionnaires (Table 1)

With respect to antisocial behaviour and omega-3 supplementation, the measurement of psychological change will focus on both the behavioural and the psychometric expression of aggression. Previous research [2] has used the *Aggression Questionnaire* (AQ) [45] to assess cognitive changes in aggression. The AQ is a self-report inventory that screens adults for aggressive tendencies, providing sufficient detail to enable treatment outcome measurement.

The benefits from essential fatty acid supplementation with ADHD are most likely with the inattentive subtype [54]. Recent models of attention deficit disorders (ADDs) have suggested that the core symptoms of ADDs are essentially cognitive [55]. Emotions have been identified as being one of the cognitive functions affected by ADDs, with the management of frustration and anger often impaired [56]. Such deficits are assessed by the *Brown Attention Deficit Disorder Scales* [46]. The BADDS has been used for ADD screening as well as the monitoring of treatment effectiveness of ADD and has been reported to have good construct and internal validity as well as discriminative power [57]. *Conners’* ADHD scales [47] have been well-validated and widely used in ADHD research including a range of omega-3 studies [33]. The 21-item Depression and Anxiety Stress Scales (*DASS-21* [49];) will be used to assess depression, anxiety and stress. Barratt Impulsiveness Scale (*BIS-Brief*) will be used to assess impulsiveness [48]. The Project Officers will assist in the delivery of psychological tests (*AQ*, *BADDS*, *Conner’s ADHD*, *DASS-21* and *BIS-Brief*) at baseline and post-intervention.

